Acute injuries [15], particularly those resulting from motor vehicle crashes [16], are major contributors to global mental health burden and disability [17,18,19], often leading to significant psychophysiological distress [20,21]. Studies show that up to 50% of individuals with acute injuries remain highly distressed six weeks after injury, increasing their risk of developing PTSD, depression, and anxiety disorders [9,10,22,23]. Dysregulated stress responses and heightened physiological arousal have also been identified as physiological stress markers in those experiencing elevated distress following traumatic injuries [20,24]. Despite its considerable impact, psycho-physiological distress associated with sustaining an injury often goes unrecognised, delaying timely support during a critical window for recovery. The Emergency Department (ED) is a critical setting for recognising acute stress, raising awareness, and initiating early psychological support, particularly for patients with minor-to-moderate injuries for whom the ED may be the only point of care. While physical stabilisation is essential, the psycho-physiological impact of trauma is equally important and should receive the same priority in ED care. Neglecting emotional consequences leaves many patients unprepared to cope, given their central role in holistic and sustained recovery [11].

ED healthcare staff face unique daily stressors, fatigue, and repeated exposure to trauma, which disrupt autonomic and circadian regulation, increasing their vulnerability to chronic stress and burnout [3,4,5,6,7,25,26]. Research has demonstrated dysregulation of stress response systems in this population, including blunted cortisol responses and autonomic imbalance [27,28]. Despite this, there is a lack of proactive and sustainable stress-management strategies that are specifically tailored to this workforce and integrated into routine clinical workflows. This highlights a critical gap in current approaches to supporting staff wellbeing and organisational resilience, both of which are essential for maintaining high-quality, safe patient care [26,29].

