## 2. Materials and Methods

### 2.1. Participants and Setting

Four groups of participants, including patients and ED healthcare workers in emergency care settings, will be recruited from the ED of Royal North Shore Hospital, a Level 1 Trauma Centre, in Sydney, Australia. Between 3 and 8 eligible participants will be recruited per group (at least 3 participants per experiment) for a total of up to 32 participants. The groups are as follows:*Sample* 1: Patients presenting to the ED with mild-to-moderate injuries (Injury Severity Score, ISS < 15).*Sample* 2: Patients presenting to the ED with severe injuries (ISS ≥ 15).*Sample* 3: Patients presenting to the ED with acute non-traumatic, minor-to-moderate medical complaints (Australasian Triage Scale, ATS category 3–5 = less urgent).*Sample* 4: Emergency healthcare workers exposed to workplace stress.

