**Experimental phases:**

Table 1 and Figure 2 provide a schematic overview of the experimental study design, phases, and timeline. Each single-case experiment, including at least three tiers, begins with a **(i) Baseline phase (usual care)** of 1–3 weeks, with duration randomised for each participant, followed by a **(ii) Intervention phase (WeCare program)** of 6 weeks. A staggered, multiple-baseline design is used: all participants start the baseline at the same time, but the intervention begins at different times (Tiers I–III)—approximately 7 days (end of the 1st week) for Tier I, 11 days (midpoint of the 2nd week) for Tier II, and 15 days (start of the 3 week) for Tier III. This ensures robust within-person controls and reducing external bias. The minimum 7-day baseline allows for the collection of at least five observations, ensuring maximum rigour [59], while accommodating day-to-day variability (e.g., “bad day”) and logistical constraints (e.g., participant availability for an in-person visit). During the Baseline phase, participants will be provided with a *smartwatch* device (Vivoactive 5, Garmin Ltd., Schaffhausen, Switzerland, https://www.garmin.com/en-AU/legal/compliance/, https://www.garmin.com/en-AU/p/1057989/; accessed on 15 October 2025), worn on the wrist for continuous physiological monitoring through the whole study. The device’s display will remain blank, and participants will not have access to any feedback or vital sign data. They will be instructed to continue their daily routines and usual care practices without changes to medication, lifestyle, or activities. To support retention and maintain engagement during the baseline phase, participants will receive one to two brief messages per week acknowledging their data collection and encouraging continued participation. Regular contact of this kind has been shown to improve adherence and reduce attrition in single-case and digital health intervention studies [60].

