Once a cohort of at least 3 eligible participants is recruited, they will be enrolled concurrently, assigned a unique study number, and booked in for the introductory session. Participants will be randomly allocated to a baseline phase duration of 1, 2, or 3 weeks (i.e., 7, 11, or 15 days, respectively) depending on their tier, in accordance with the study’s single-case design standards. An independent researcher, not involved in participant recruitment, will generate a randomisation sequence using standard computerised methods to minimise bias. Randomisation will take place after the pre-baseline data is collected (Week 0) to reduce the risk of allocation bias. Investigator blinding is not feasible due to study procedures, and this is not a randomised clinical trial.

All participants who choose to enrol in the study will be automatically included in all three components of this proof-of-concept study. Upon completion of the *WeCare* program as the experimental component, research investigators will invite participants to take part in in-depth interviews. Additionally, cost data will be collected weekly throughout the duration of the study.

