**(b)** 
**Primary outcome measures**

Primary outcomes are the target behaviours directly addressed by the intervention. These are assessed daily, throughout the baseline and intervention phases (including at enrolment, Week 0), post-intervention (within 2 weeks of the final session), and at 3- and 6-month follow-ups. They include the following clinical self-report (daily diary) and psychophysiological outcomes of stress regulation, selected for their sensitivity to change and appropriateness for single-case designs.

**
*Clinical self-report outcomes:*
**
*Psychological distress*: Daily ratings of 24 h average distress measured with the 1-item Subjective Units of Distress Scale (SUDS), ranging from 0 (no distress) to 100 (extreme distress) [69], plus ecological momentary assessments every 2 h for 4 days only (2 during baseline and 2 during intervention).*Sleep quality*: Measured each morning using a single-item scale from 0 (worst) to 10 (best), aligned with self-reported wake times to minimise recall bias.
***Psychophysiological outcomes*:** Continuously recorded via a smartwatch using photoplethysmography and an accelerometer. Adherence and data completeness will be monitored via app analytics and automated tracking tools.
*Heart rate variability (HRV) metrics*: Reflects autonomic nervous system (ANS) activity. Higher parasympathetic (vagal) tone indicates improved regulation, whereas low HRV is associated with mental health risk [37,38,39]. HRV Root Mean Square of Successive Differences (HRV-rMSSD) and other time-, frequency-, and nonlinear-domain and composite metrics will be extracted from beat-to-beat intervals, especially during overnight monitoring.*Sleep parameters*: Includes sleep duration, bedtime, sleep onset latency, nocturnal heart rate, wake-up time, and sleep-related temperature deviation (if available).

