**Figure 3 sensors-26-00104-f003:**
[figure not shown]
WeCare program: weekly themes, suggested activities, and reflection prompts.

**Table 1 sensors-26-00104-t001:** Detail of experimental phases.

Phase	When It Starts	How Long	Device Used	What Happens
Baseline (Usual care)	*Sample* 1 and 3: 0–2 weeks post-ED care. *Sample* 2: 4–6 weeks post-ED care. *Sample* 4: Any time.	1–3 weeks (7, 11, 15 days by tier)	“Blinded” smartwatch (wrist device)	- In-person onboarding. - Wear smartwatch daily. - Smart ring sized for next phase. - Continue usual care, no changes. - Daily diaries and weekly surveys.
WeCare Program (Intervention)	After baseline phase ends	6 weeks (staggered by tier)	“Blinded” smartwatch Smart ring	- In-person onboarding. - Continue smartwatch monitoring. - Start intervention using a digital health platform and a smart ring as companions to track real-time physiological data and receive personalised education/feedback.
Optional Extension (Device testing)	After intervention phase ends	2 weeks	“Blinded” smartwatch	- Smartwatch (instead of smart ring) as intervention companion. - Test delivery method only. - Part of qualitative, co-design acceptability analysis.

**Table 2 sensors-26-00104-t002:** Participants’ inclusion and exclusion criteria.

Participant Group	Inclusion Criteria	Exclusion Criteria

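### For ED staff (Sample 4), a 7–15 day baseline starting at any time does not ensure that shift mix is balanced with the program phase, and no daily shift item is listed to adjust for it

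*Protocol article*

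**What the plan says.** - **Timing.** Table 1 lets staff begin baseline without an anchor ("Sample* 4: Any time"). Baseline length is "1–3 weeks (7, 11, 15 days by tier") and the program lasts "6 weeks (staggered by tier"). Section 2.4 assigns the length by chance: "Participants will be randomly allocated to a baseline phase duration of 1, 2, or 3 weeks". Roster plays no part in the allocation.
- **Who.** Section 2.1: "Between 3 and 8 eligible participants will be recruited per group". Table 2 admits doctors, nurses, paramedics and allied health staff of the ED, with no criterion on shift type or roster.
- **Outcomes.** Under the primary outcome measures in Section 2.6.2, HRV metrics "will be extracted from beat-to-beat intervals, especially during overnight monitoring". Sleep duration, bedtime, wake-up time and nocturnal heart rate are also primary, as are daily distress (SUDS, 0–100) and morning sleep quality.
- **What is listed.** Table 3 has no shift, roster or work-schedule row. The nearest items are the weekly diary of adverse events and stressors and, in Section 2.6.4, weekly time off work.
- **The protocol's own premise.** The Introduction describes daily stressors, fatigue and "repeated exposure to trauma, which disrupt autonomic and circadian regulation" in ED staff.
- **The safeguard offered.** Section 2.2.1: "The minimum 7-day baseline allows for the collection of at least five observations". The same passage presents this minimum as room for ordinary variation from day to day.

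**The concern.** Each staff member is their own control, and the level, slope and overlap analyses in Section 2.8 compare phases within the person. If nights make up a different share of baseline and program days, that difference goes straight into the individual's contrast. A run of nights is several consecutive days, so a 7-day minimum chosen to absorb a single bad day does not absorb it. For someone on nights, a recording made during the night is also a different measurement: on duty rather than asleep.

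Sample 4 is one of three systematic replications, with 3 to 8 people. A spurious or masked individual effect there affects what the study can say about replication in staff. An analysis plan can choose a covariate, but it cannot adjust for a daily shift type that nobody recorded.

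**Working it through.** The plan gives no power figure, SD, effect size or roster, so there is no stated number to reproduce. What can be computed is how far shift mix can differ between phases under assumed rosters.

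**Inputs from the document:** baseline B = 7, 11 or 15 days; program 6 × 7 = 42 days; start unrelated to roster; significance level 0.05 (taken as two-sided).

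**Assumed inputs:** one block of k consecutive nights per roster cycle, every start day equally likely; independent daily errors with SD 1; a night day shifts the outcome by 0.5 or 1.0 SD.

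**Step 1. Imbalance.** D = (nights in baseline ÷ B) − (nights in program ÷ 42).

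For k = 4 in 28 days, the extremes by hand are:
- No night in baseline, two blocks in program: 0 − 8/42 = −19 points (any tier).
- Whole block in baseline, one block in program: Tier I 4/7 − 4/42 = 57.1 − 9.5 = +48; Tier II 4/11 − 4/42 = 36.4 − 9.5 = +27; Tier III 4/15 − 4/42 = 26.7 − 9.5 = +17.

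Over all 28 start days:

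| Roster | Tier | Range of D (points) | Mean D | Baseline with no night |
|---|---|---|---|---|
| 4 in 28 | I | −19 to +48 | 0 | 64% |
| 4 in 28 | II | −19 to +27 | 0 | 50% |
| 4 in 28 | III | −19 to +17 | 0 | 36% |
| 7 in 28 | I | −33 to +83 | 0 | 54% |
| 7 in 28 | II | −33 to +47 | 0 | 39% |
| 7 in 28 | III | −33 to +30 | 0 | 25% |

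For 4 in 28, |D| is at least 10 points on 79%, 86% and 86% of start days (Tiers I, II, III) but below 20 points on 79%, 71% and 100%. The +48 extreme occurs on 4 of 28 start days (14%).

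**Step 2. A roster that does balance.** Two nights in every 7 days gives 12/42 = 28.6% in the program. Tier I: 2/7 − 12/42 = 0. Tier II: from 2/11 − 12/42 = −10 to 4/11 − 12/42 = +8. Tier III: from 4/15 − 12/42 = −2 to 5/15 − 12/42 = +5.

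**Step 3. On the distress scale.** Suppose, as an illustration only, that SUDS is 20 points worse on night days. With an inert program, Tier I on the 4-in-28 roster shows anything from an apparent improvement of 0.476 × 20 ≈ 10 points to an apparent worsening of 0.190 × 20 ≈ 4 points.

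**Step 4. False positives with no program effect.** Simulated test of level change in one person, without a shift term; range across the three tiers:

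| Roster | No shift effect | 0.5 SD | 1.0 SD |
|---|---|---|---|
| 4 in 28 | about 5% | about 5–6% | about 6–7% |
| 7 in 28 | about 5% | about 7% | 10.5–11.7% |

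On the 7-in-28 roster at 1.0 SD:
- With a daily shift indicator in the model, the single-case rate returns to 4.8–5.6%.
- A pooled model with one common phase effect gives about 12% for 3, 6 or 8 staff.
- A two-stage analysis of the per-person effects stays near 5%.
- Mean bias over random start days is about zero.

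**The case against.** **The missing item may be collected.** Table 3 lists outcomes, and it omits other things the study gathers, such as self-reported wake times and the cost diaries. The daily diary form is not printed in the article. This stands: one can say only that no shift item is listed. A reader might infer that shift data are certainly not collected; the article does not show that.

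**Nights can be inferred.** Bedtime, wake-up time and continuous activity from the watch would reveal much night work, so it would be wrong to say that the shift mix is lost. But these are partial proxies, and bedtime and wake-up time are primary outcomes. Adjusting for them could remove real program effect.

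**HRV is not tied to a clock window.** The wording favours overnight recording without fixing hours, so extraction from the main sleep episode is open. This also stands. The point is to state that choice for staff.

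**The start rule is innocent.** The other entries in that Table 1 column count time from ED care, which staff do not have. That explains the wording, but leaves the start unrelated to roster.

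**The stagger guards against shared rosters.** If colleagues share a run of nights, it falls on the same calendar dates, while program starts are randomised and staggered. Change would then fail to follow each person's start. This is a partial guard at the level of the experiment. It does not protect each person's own contrast.

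**The sizes are assumed, in a pilot.** Some eligible staff may work no nights, the large imbalances are not the typical ones, and effectiveness is a preliminary aim. All true, and it limits the weight of the point.

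**Conclusion.** The point holds in a limited form. The staff schedule does not ensure that shift mix is balanced between phases, and no daily shift measure is listed, so roster differences can produce or mask individual phase changes in HRV, sleep and distress.

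Two stronger readings are not supported. One is that the design cannot balance shifts: a fixed weekly roster would be nearly balanced. The other is that results for staff would be biased towards benefit: over random start dates the mean imbalance is zero, and a two-stage summary keeps its error rate near 5%. The harm is to individual effects, and to a pooled model that assumes one common phase effect.

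The inflation of single-case false positives is small on a 4-in-28 roster (about 5–7%) and clearer on a 7-in-28 roster with a 1 SD shift effect (about 11–12%). These figures rest on the assumed rosters, shift effects and independent daily errors. This is worth correcting because it is cheap, and because shift type is hard to restore cleanly once data collection is over.

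**What to change.** For Sample 4 only:

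1. Add one item to the existing daily diary: day shift, evening shift, night shift or off.
2. State that HRV and sleep metrics are extracted from the main sleep episode in each 24 h, whatever the clock time.
3. Include shift type as a daily covariate in the level- and slope-change analyses and the mixed models, and mark it on the individual graphs.

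If the full protocol's diary already records shift type, item 1 reduces to naming it.

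The cost is one extra tap a day, one extraction rule and one covariate for at most 8 participants. Where few days of a shift type fall in baseline, the adjusted contrast will be less precise; the graphs will show where this is so. Nothing in the intervention changes.

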**(c)** 
**Generalisation measures**

Generalisation measures aim to assess broader impacts of the intervention on participants’ lives.

**‘Proximal’ generalisation measures**

Assessed *weekly* throughout the baseline and intervention phases (including at enrolment, Week 0), post-intervention (within 2 weeks of the final session), and at 3- and 6-month follow-ups (~15 min per completion). They include the following clinical self-report and physiological measures.

***Clinical self-report outcomes*:**

*Mental health:*
○Perceived Stress Scale (PSS) [70].○Patient Health Questionnaire-9 (PHQ-9) [71].○PTSD Checklist for DSM-5 (PCL-5) [72].○Generalised Anxiety Disorder Scale (GAD-7) [73].
*Sleep quality*: Pittsburgh Sleep Quality Index (PSQI) [74].*Consumer perception of change*: A 15-point Global Impression of Change Scale (−7 to +7).*Overall health status*: EQ-5D visual analogue scale (0–100).
***Psychophysiological outcomes*:** Continuously monitored via a smartwatch, including heart rate, respiratory rate, blood oxygen saturation (SpO_2_), activity metrics (e.g., steps, movement, calories, and circadian rhythm), and daily health summary metrics related to stress and daytime and night-time recovery.

**‘Distal’ generalisation measures**

Assessed at pre-intervention, post-intervention (within 2 weeks of final session), and at 3- and 6-month follow-ups. These aim to assess broader impacts of the intervention on participants’ lives (~15 min per completion) and include measures of general wellbeing, pain interference, social participation, and perceived benefits, etc.

#### 2.6.3. Acceptability and Usability

Acceptability and usability based on user experience of the WeCare program will be evaluated as part of the co-design component that will commence following the conclusion of the WeCare program. The focus is on perceived benefits, unintended effects, challenges encountered, and potential solutions, as reported by each participant group in the study. To guide this evaluation, the “Theoretical Framework of Acceptability (TFA)” [75,76] will be applied. Using the TFA at this stage enables a structured assessment of both anticipated and experienced acceptability for both the recipients and deliverers of the intervention. This will support evidence-informed decisions about refining the program’s form, content, and delivery mode.

Given that this is the first piloting of the WeCare program, the TFA will play a crucial role in identifying whether early expectations align with actual user and provider experiences. Where applicable, adaptations to intervention components (e.g., due to lower-than-expected recruitment or higher attrition) will be explored based on insights from this phase. Acceptability will be operationalised across the seven TFA constructs using a sequential mixed-methods approach, which allows key patterns identified in the quantitative data to be further explored and contextualised through qualitative insights.

*Quantitative methods*: Questionnaires or visual analogue rating scales aligned with TFA constructs will assess anticipated acceptability among potential deliverers and recipients.*Qualitative methods:* Semi-structured interviews or focus groups, guided by the seven TFA constructs, will explore participants’ and stakeholders’ lived experiences of the intervention. These qualitative methods will offer in-depth insights into barriers, facilitators, and contextual factors influencing engagement, adherence, and perceived value, factors often not captured through quantitative means alone.

Participants from the quantitative phase will be invited. In the instance of too many (>10) participants expressing interest in the qualitative phase, researchers will select a sample of 6–10 through discussion, ensuring that at least one participant from each group is included, in line with the recommended sample size by Braun and Clarke [77]. To minimise bias, interviews will, where possible, be conducted by independent researchers who were not involved in delivering the intervention, so that interviewees are unfamiliar with the interviewers. All interviews will be audio-recorded and transcribed verbatim. The transcribed interviews will be analysed using the six-phase approach outlined by Braun and Clarke [77,78], which combines both deductive and inductive processes. This means that while data collection and analysis will be guided by the TFA framework, the process will remain open to novel and emerging concepts arising from the data. Findings from this qualitative phase will directly inform refinement of the *WeCare* program and its future implementation strategies.

#### 2.6.4. Cost Benefits

A nested Cost analysis of the WeCare program will be conducted using weekly self-report diaries collected throughout the study. Data will include *healthcare utilisation* (e.g., medical appointments, hospital visits, treatments, medications, and diagnostics) and *work-related costs* (e.g., time off work due to stress, injury, or illness). The analysis will assess whether the wearable-based intervention reduces healthcare use and work absenteeism. This will inform the economic benefits of implementing the WeCare program as a scalable solution.

### 2.7. Sample Size

Up to 32 participants will be recruited for this pilot study, up to 8 participants in each study group. Power calculation is not relevant as this is an N-of-1 pilot study using a design that has not been utilised previously.

### 2.8. Data Analysis and Reporting

For the primary measures, graphical representation and calculation of a mean and trend line will be used to analyse changes over time and between periods. Trend analyses will also be conducted to account for unstable baselines (e.g., increasing or decreasing severity over time), providing a more nuanced understanding of change. Level- and slope-change analyses will be used to further analyse change between periods. Secondary analyses will be performed on secondary outcomes. No interim analyses will be performed in this study. The level of significance to be used will be set at *p* < 0.05 unless otherwise required. The quality of the dataset will be inspected regularly by outcome assessors for missing data. Additionally, missing or spurious data will also be inspected by one of the senior researchers. Moreover, linear mixed-effects modelling [79], a multiple regression technique that is flexible and suitable for single-case design studies, will be used to provide standardised effect sizes and measures of statistical significance. Analyses will also include evaluation of overlap between phases; for example, Tau-U will be applied as a non-parametric effect size method appropriate for single-case experimental designs.

A feasibility analysis will be also conducted using prespecified progression criteria to help guide the interpretation of pilot trial findings to decide whether, and how, a definitive RCT is feasible and should be conducted. Once all the text information from interviews is collated, qualitative data analysis will be conducted, which involves thematic analysis and directed content analysis to determine the most important themes that emerged from the participant discussions regarding the acceptability of the intervention. A summary of the results will be sent to the participants for checking, verification, and confirmation of the researcher’s interpretation of key issues and thematic understanding. The software package NVIVO will be used to analyse the qualitative data.

To ensure clarity and transparency in reporting, study findings reporting will adhere to the Single-Case Reporting guideline In BEhavioural interventions [80] and Consort Extension for reporting N-of-1 trial guidelines [81], while the qualitative component will be reported following the Consolidated Criteria for Reporting Qualitative Research (COREQ), a 32-item checklist for interviews and focus groups [82].

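### In Tier I the baseline is one week long, so unadjusted trend, level-change and slope-change estimates depend on the start weekday if a weekly cycle exists

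*Protocol article*

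**What the plan says.** Section 2.8 (Data Analysis and Reporting) says that for the primary measures "graphical representation and calculation of a mean and trend line will be used to analyse changes over time and between periods". It adds trend analyses to deal with unstable baselines, and then: "Level- and slope-change analyses will be used to further analyse change between periods". A linear mixed-effects model and Tau-U are also planned. The article does not list the model's covariates.

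The data for these analyses are daily. Section 2.6.2, on the primary outcome measures, says: "These are assessed daily, throughout the baseline and intervention phases". They include a distress rating, a sleep rating, bedtime, wake-up time, sleep duration and heart rate variability.

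Baseline length is "7, 11, or 15 days, respectively" by tier (section 2.4), and section 2.2.1 places the program start at "approximately 7 days (end of the 1st week) for Tier I, 11 days (midpoint of the 2nd week) for Tier II, and 15 days" for Tier III. On the shortest baseline, section 2.2.1 says: "The minimum 7-day baseline allows for the collection of at least five observations". Table 1 gives the program as "6 weeks (staggered by tier", which is 42 days.

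Within an experiment "all participants start the baseline at the same time" (section 2.2.1). Under section 2.4, participants state a preferred day for the introductory session and are booked in. The element that is randomised is baseline length.

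**The concern.** A line fitted to exactly one week cannot separate a weekly cycle from a trend. Seven consecutive days always contain one Saturday and one Sunday, so the weekend share is the same in baseline and program. The position of those two days within the week still sets the fitted slope: last for a Monday start, first for a Saturday start.

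The level-change contrast projects the baseline line to the switch, and the slope-change contrast subtracts the baseline slope, so both inherit this artefact. Trend analysis is the plan's guard against unstable baselines. In Tier I it could create an instability that the data do not have.

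Randomising baseline length does not remove this from a Tier I series, because the start weekday is fixed by booking before allocation. These are N-of-1 trials, so each series is also read in its own right. At stake is whether a single-case Tier I result reflects the program or the calendar.

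**Working it through.** The article states no power, effect size or error rate to reproduce, so the check is direct.

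**Inputs.** From the article: baselines of 7, 11 and 15 days; a 42-day program; one value per day; significance at 0.05 (taken as two-sided). Assumed: a weekend-minus-weekday difference d of 0.25 to 1.0 daily SD, no true program effect, and independent daily errors unless stated.

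**Model.** Outcome = intercept + time + phase + phase × time since the switch, fitted by least squares to a series that is d on Saturday and Sunday and 0 otherwise.

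**Tier I by hand, Monday start.**
- Baseline days centred at -3 to +3 have sum of squares 28. Saturday is at +2 and Sunday at +3, so the slope is (2 + 3)/28 = 0.179d per day.
- Baseline mean is 2/7 = 0.286d. Projected to day 8, four days past the centre: 0.286 + 4 × 0.179 = 1.000d.
- The program line over 42 days has slope 0.0049d per day. Its value on its first day is 0.286 - 20.5 × 0.0049 = 0.186d.
- Level change: 0.186 - 1.000 = -0.81d. Slope change: 0.005 - 0.179 = -0.174d per day.

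Other starts follow by moving the weekend: Tuesday 3/28, Wednesday 1/28, Sunday (-3 + 3)/28 = 0, with Thursday, Friday and Saturday as mirror images.

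**False level change, in units of d:**

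| Start | Tier I | Tier II | Tier III |
|---|---|---|---|
| Monday | -0.81 | +0.11 | -0.27 |
| Tuesday | -0.49 | +0.26 | -0.12 |
| Wednesday | -0.16 | -0.10 | +0.04 |
| Thursday | +0.16 | -0.40 | +0.19 |
| Friday | +0.49 | -0.14 | +0.35 |
| Saturday | +0.81 | +0.12 | +0.10 |
| Sunday | 0.00 | +0.14 | -0.29 |

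The largest false slope change is 0.174d per day in Tier I, 0.037d in Tier II and below 0.03d in Tier III.

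**Direction.** If distress dips at weekends, d is negative. A Saturday start then shows false benefit and a Monday start false harm. With an assumed 10-point dip on the 0–100 distress scale, a Saturday start gives a false level change of 0.814 × (-10) = -8.1 points.

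**Against noise.** The Tier I level-change standard error is √(1/7 + 16/28 + 1/42 + 20.5²/6170.5) = √0.806 = 0.898 SD, where 6170.5 = 42 × (42² - 1)/12. Worst-day bias at d = 0.25, 0.5 and 1.0 SD is 0.20, 0.41 and 0.81 SD. At 0.5 SD this is 0.41/0.898 = 0.45 standard errors.

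Simulated worst-day false-positive rates in Tier I are about 5% with no cycle, 7% at 0.5 SD and 10–11% at 1 SD. With lag-1 correlation of 0.3 the level is already about 10% with no cycle and about 16% at 1 SD.

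**Other planned analyses.**
- Tier I phase means over complete weeks: 2/7 in both phases, bias exactly 0. If only five of the seven baseline days are observed, the bias can range from -0.11d to +0.29d.
- Tau-U in Tier I at 1 SD: moves by at most 0.02.
- Pooled three-tier fit with participant intercepts: level bias at most 0.18d (standard error 0.382 SD), slope change at most 0.029d per day (standard error 0.046). False positives are about 3–7% at 1 SD.

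**With a weekend term.** The bias is 0 for every start weekday. At 1 SD with independent errors, Tier I false positives return to about 4–6%. The level-change standard error rises at most from 0.898 to 0.938 (4.5%) in Tier I, 0.714 to 0.724 (1.4%) in Tier II and 0.622 to 0.631 (1.4%) in Tier III.

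**The case against.** The strongest reply is that this is analysis-plan detail. The article names a flexible mixed model without listing covariates, and the full plan may already hold a weekday term. That stands to this extent: a reader might infer that the plan deliberately fits unadjusted daily values, but the article says only that trend lines and level/slope changes will be estimated, with no weekday adjustment stated. What the article does fix is the combination that causes the problem: a one-week baseline, a trend fitted within it, and contrasts built on that trend.

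The size of d is also unsupported. No section reports a weekly cycle. Recently injured or ill patients may be off work, and emergency staff on shifts need not follow the calendar week. This stands, and the point is therefore conditional.

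A reader might further infer that the trial's overall effectiveness result is biased, or that every cohort member shows the same false effect. The numbers do not support either. Cohort members share the calendar but not the bias, because the tiers switch on different weekdays; all three agree in sign only for a Saturday start. The pooled estimate moves little, and Tau-U and the complete-week Tier I mean essentially not at all. Repetition across experiments would need sessions to fall habitually on the same weekday, which the article does not say.

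Finally, effectiveness is described as preliminary, and the article concedes limited ability to detect effects. That lowers the stakes, but single-case Tier I results would still be reported.

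**Conclusion.** The point holds in conditional form. If a weekend-weekday difference exists and is not modelled, single-case Tier I trend, level-change and slope-change results depend on a start weekday that is shared and not randomised. The false level change lies between -0.81d and +0.81d. It is zero for a Sunday start and about 0.16d in size for Wednesday or Thursday. It can point to harm as easily as to benefit.

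At d = 0.5 SD the effect is modest, under half a standard error. It becomes material in Tier I at about 1 SD. Elsewhere it is smaller: level bias is at most 0.40d in Tier II, 0.35d in Tier III and about 0.18d pooled.

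These figures assume a calendar-weekend pattern, complete daily data, exact 7-, 11- and 15-day baselines (the article calls them approximate) and, except where stated, independent errors. This is a cheap improvement to make, not a flaw that undermines the study.

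**What to change.** In section 2.8, state that the models giving trend, level-change and slope-change estimates for daily outcomes include a weekend/weekday indicator; for emergency staff, use work day versus day off if that is recorded. The term can be estimated from the whole series of 49 to 57 days (7 + 42 to 15 + 42), so one baseline weekend is enough.

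Also state that Tier I conclusions will not rest on an unadjusted 7-day trend line. The complete-week mean contrast and Tau-U can be shown beside it.

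The cost is one model term and, provided daily records carry their date, no new data for the weekend version. The level-change standard error rises by up to about 4.5% in Tier I and 1.4% in Tiers II and III. The term does not deal with serial correlation, which inflates false positives separately.
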